**Intervention content:**

Provide patients with detailed information about the functions of Artificial Intelligence-Empowered Mobile Health, demonstrate its operation, and guide AI questioning.

**Specific Methods:**

1. Detailed Description of Functions:

Artificial Intelligence-Empowered Mobile Health provides the following support:

① Health Education: Answers questions about diseases, such as preoperative preparation, potential complications, recovery time, etc., guides physical recovery, such as the normal range of bleeding days and amounts, indications for medical treatment, etc., provides dietary advice, such as dietary taboos, common dietary misconceptions, etc., provides exercise guidance, such as bed rest time, appropriate types of exercise and timing, etc.

② Entertainment and Emotional Support: Artificial Intelligence-Empowered Mobile Health has personification attributes, can introduce itself during the first interaction, can recognize user emotions and provide comfort and encouragement, and also provides practical tools such as weather queries and simple calculations.

2. Artificial Intelligence-Empowered Mobile Health Usage Process Guidance:

Step 1: Researchers provide one-on-one guidance to patients who meet the criteria and have signed the informed consent form, instructing them to follow the WeChat Official Account for this study on their mobile phones.

Step 2: Guide patients to enter the Official Account and locate the chat interaction page.

Step 3: Under the guidance of the researcher, patients take the lead in operating the Official Account, using text or voice input to experience its health education and emotional support functions.

3. Question Guidance:

Researcher demonstrated common input commands face-to-face, such as “What do I need to prepare for an abortion?” and guided patients on how to ask questions effectively to the Official Account. The researcher provided concise answers to other questions from patients about the system’s functions and operation, and performed live demonstrations of the functions on the patients’ mobile phones.

**Swanson’s Theory of Caring:** Being with, Maintaining belief.

**Intervention providers:** Attending doctor, researcher.

**Intervention content:**

Emotional Presence: Introduce relevant personnel and treatment processes, assist families in need, and convey a sense of companionship.Give Courage: Share cases to alleviate patients’ fears.

**Specific Methods:**

Staff Introduction: Introduce the attending doctor and nurse during the first consultation to establish comfort and familiarity.Detailed Explanation: Provide an everyday language explanation of the purpose of the examination and important considerations. For example, a blood routine is conducted to exclude anemia and ensure safety, and an ultrasound requires holding urine and drinking water beforehand. Visualize medical reports, such as describing “a gestational sac size of 5 cm” as “the size of an egg, consistent with the gestational age.”Body Language: Use eye contact, physical touch, and accompany patients during waiting periods to alleviate anxiety and feelings of loneliness.Provide Support Tailored: Explain medical insurance policies and exemption procedures in person for economic difficulties, provide dialect interpretations (with QR codes) and handwritten versions of important notes for those with lower educational levels.Empowerment Through Similar Cases: Provide successful case examples with similar clinical and social backgrounds to enhance patients’ confidence and courage in recovery.

**Phase 2: Two weeks after surgery and before follow-up examination**.

**Swanson’s Theory of Caring:** Knowing.

**Intervention providers:** Attending doctor, researcher.

**Intervention content:**

Assess postoperative complications, physical recovery status, and current psychological state.

**Specific Methods:**

Communication Time: One week after the patient’s abortion, online communication via telephone, WeChat, or other platforms, lasting approximately 20 minutes.Communication Content: Comprehensive understanding of the patient’s physical recovery, inquiring about fever, foul-smelling secretions, bleeding, abdominal pain, etc., assessing the patient’s psychological state, whether there are negative emotions such as inferiority, anxiety, depression, or despair, recognizing the patient’s additional needs for post-operative health knowledge.

**Swanson’s Theory of Caring:** Doing for, Enabling.

**Intervention providers:** Researcher.

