#### Control group: standard care

2.5.1

The control group was not completely blank. At the time of enrolment, patients in the control group received standard oral health education, including explanations of the surgical procedure and precautions, routine preoperative examinations, and guidance on postoperative precautions. Any questions or concerns raised by patients were answered in detail.

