**Specific Methods:**

Check the Official Account function before 8:00 every day to ensure that the AI response is working properly.Send brief post-operative guidance and education via WeChat at 9:00 every day, and guide consultations through questions about common misconceptions. For example: “Is it true that you can’t eat fish after an abortion?” Please consult “Xiao Yu” (the name of the Artificial Intelligence-Empowered Mobile Health agent) for an authoritative answer!Review patient-AI interaction records by 9:00 PM daily, summarize key feedback for the attending doctor, and simultaneously update the knowledge base with missing content.

**Swanson’s Theory of Caring:** Being with, Maintaining belief.

**Intervention providers:** Researcher.

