The Posttraumatic Stress Disorder (PTSD) Checklist for DSM-5 (PCL-5) is used to measure symptoms that meet the criteria of the DSM-5. The scale consists of four dimensions: intrusive symptoms, avoidance, cognitive/emotional negative changes, and hyperarousal, with a total of 20 items. Each item is scored on a scale of 0 to 4 (0 = “not at all” to 4 = “extremely “). The total score range is 0–80 points, with higher scores indicating more severe PTSD symptoms and greater functional impairment. The overall Cronbach’s alpha for the original scale was 0.94 (41).

Quality of life is measured using the EuroQol Visual Analogue Scale (EQ-VAS), which is used to assess the overall health status of participants. The EQ-VAS is a vertical scale on which respondents record their self-rated health status (42). The scale ranges from 0 to 100, with 0 representing “the worst health state you can imagine” and 100 representing “the best health state you can imagine”.

Physiological and biochemical data: Professional medical staff at the Inner Mongolia Maternity and Child Health Care Hospital, who are qualified to perform such procedures, strictly adhere to clinical operating procedures and hospital testing standards to conduct human chorionic gonadotropin (HCG) level measurements and ultrasound examinations on patients. The HCG level measurement employs chemiluminescence immunoassay, utilizing the advanced, fully automated chemiluminescence immunoassay analyzer to precisely quantify the level of human chorionic gonadotropin in serum. Ultrasound examinations are conducted using a color Doppler ultrasound diagnostic instrument, with experienced ultrasound specialists conducting detailed examinations and assessments of uterine morphology, endometrial thickness, and the presence of any residual material within the uterine cavity.

Qualitative interview: Researchers initially developed a semi-structured interview outline based on the research objectives and a review of relevant literature. After consulting with qualitative research experts and conducting preliminary interviews, the research team revised the interview outline based on expert discussions and finalized the content of the interview outline. During the interviews, researchers needed to maintain a certain degree of openness and flexibility. The outline included, but was not limited to, the following questions:

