The Data Monitoring Committee (DMC) consists of at least two members of the Ethics Committee of the Inner Mongolia Maternal and Child Health Hospital, who have no conflict of interest with the study. The DMC is responsible for conducting regular monitoring independently of the principal investigator and reporting to the Ethics Committee. It has the authority to suspend or terminate any study that deviates from the protocol. The Ethics Committee reviews the progress of the study and compliance with the protocol every six months. The research team must immediately report any serious adverse events (SAEs) or adverse events (AEs). If a participant experiences a serious adverse event, researchers must report it within 24 hours and halt the trial. In the event of a severe error in the intelligent agent or significant interaction issues, the trial must also be immediately suspended. The study may resume only after technical repairs and interface improvements have been confirmed. A pre-trial validation of the intelligent agent’s performance is conducted prior to study initiation, and all investigators undergo rigorous training and certification. In a standardized environment, investigators guide participants one-on-one to scan a QR code and complete a unified electronic questionnaire, explaining questions without prompting answers. Prior to the interview, participants are fully informed of the purpose, right to withdraw, and confidentiality measures. After obtaining signed informed consent, the interview is recorded and conducted in a private setting at the pre-agreed time. During the interview, investigators flexibly guide the conversation, listen attentively, and avoid subjective evaluations. In this study, we will utilize the “Wenjuanxing” (Questionnaire Star) online survey platform for questionnaire completion to ensure data accuracy. Before data analysis, we will conduct strict data organization and cleaning.

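### As described, complications are actively sought between surgery and T1 in the intervention arm only, so reported adverse events may look more frequent there through detection alone

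*Protocol article*

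**What the plan says.** Section 2.5.4, Phase 2, lists this among the intervention content: "Assess postoperative complications, physical recovery status, and current psychological state". The method is a scheduled contact: "One week after the patient’s abortion, online communication via telephone, WeChat, or other platforms, lasting approximately 20 minutes". Its content includes "inquiring about fever, foul-smelling secretions, bleeding, abdominal pain, etc", together with psychological state and further information needs.

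The same arm has further channels. Daily in Phase 2, researchers are to "Review patient-AI interaction records by 9:00 PM daily, summarize key feedback for the attending doctor". Section 2.5.3 adds regular analysis of the interaction data to pick up severe physical and psychological symptoms, with the attending physician contacted when needed.

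For controls, section 2.5.1 says: "At the time of enrolment, patients in the control group received standard oral health education". It adds that questions raised by patients were answered. It describes no contact between surgery and the two-week visit.

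Section 2.9 (Study management) applies to everyone: "The research team must immediately report any serious adverse events (SAEs) or adverse events (AEs)". Section 2.1 places the common assessments at baseline and two weeks. Table 1 has no adverse event row.

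**The concern.** A reporting duty yields comparable records only if events come to light in the same way in both arms. Here the duty is common, but the described means of finding events between surgery and T1 belong to one arm. A short fever or a spell of bleeding that settles before two weeks would probably be recorded for an intervention woman asked at one week. For a control woman it would come to light only if she raised it herself or it emerged at the T1 visit.

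What is at stake is the safety description of an AI health service. If reported events are tabulated by arm, the service could appear to carry an excess of complications that reflects only closer questioning. Non-serious events are the most exposed, because they depend most on someone asking.

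**Working it through.** The article states no complication rate and no detection probability, so there is no figure to reproduce. The check has two parts.

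**1. Described routes by which a complication can become known, surgery to T1**

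| Route | Intervention | Control |
|---|---|---|
| Scheduled symptom enquiry at one week (2.5.4, Phase 2) | yes | not described |
| Daily review of AI logs, summarised for the doctor (2.5.4, Phase 2) | yes | not applicable, no AI access |
| Analysis of interaction data for severe symptoms (2.5.3) | yes | not applicable |
| Examination at two weeks (2.1, Table 1) | yes | yes |
| Duty to report events (2.9) | yes | yes |

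The two common routes are the T1 visit and the reporting duty. The active routes before T1 are all in one arm.

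**2. Illustration of direction and possible size**

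Inputs: 50 women per arm (section 2.2). Everything else is assumed: a true complication rate *p*, equal in both arms, of 10% to 30%; detection *d*_I of 90% to 100% in the intervention arm; detection *d*_C of 30% to 70% in the control arm.

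Expected recorded events per arm = 50 × *p* × *d*. The recorded ratio is (50 × *p* × *d*_I) / (50 × *p* × *d*_C) = *d*_I / *d*_C, which does not depend on *p*.

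- Mildest case, *p* = 10%, 90% against 70%: 50 × 0.10 × 0.90 = 4.5 and 50 × 0.10 × 0.70 = 3.5; ratio 0.90/0.70 = 1.29.
- Middle case, *p* = 10%, 95% against 60%: 50 × 0.10 × 0.95 = 4.75 and 50 × 0.10 × 0.60 = 3.0; ratio 0.95/0.60 = 1.58.
- Most extreme case, *p* = 30%, 100% against 30%: 50 × 0.30 × 1.00 = 15 and 50 × 0.30 × 0.30 = 4.5; ratio 1.00/0.30 = 3.33.

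The chance of a nominally significant two-sided 5% difference, from a power calculation for two proportions with 50 per arm, runs from about 6% in the mildest case to about 76% in the most extreme. At *p* = 10% it stays between about 6% and 29% across the assumed detection values. With a low event rate, the likelier harm is therefore a misleading table, not a false significant test.

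With the same enquiry in both arms, *d*_I = *d*_C and the ratio is 1, whatever the level of detection.

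**The case against.** **Adverse events are not a listed outcome.** This is correct. Section 2.6 and Table 1 do not include them, and section 2.7 plans no comparison of them by arm. Section 2.9 uses them for oversight. It limits the weight of the point but does not remove it, since the reports will exist and may be summarised by arm.

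**A condensed article may leave adverse event collection to the full protocol.** This is also fair, and the most that can be said is that nothing equivalent is described for controls. The point does not rest on a missing form, however. The article itself assigns complication enquiry to one arm. A fuller document would resolve this only by giving controls the same enquiry or by confining comparisons to a common source.

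**The magnitude is assumed.** It is. Under the middle case above the gap is fewer than two events.

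A reader might also infer more than the document supports:

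- *That the T1 ultrasound and HCG are ascertained differently by arm.* They are not. Table 1 gives one time point without distinction by arm, section 2.6.2.1 gives one automated assay and one ultrasound procedure, including "the presence of any residual material within the uterine cavity", and section 2.1 states that the staff doing these examinations are unaware of allocation. If tissue is found at the call and dealt with before T1, a clear cavity at T1 is an effect of the package being tested. Counting such cases as events would bring unequal detection into an outcome now measured alike.
- *That the arms cannot be compared for harm.* This is too strong, because a common enquiry at T1 would allow a comparison.
- *That the rule halting the trial after a serious event is biased.* Events needing hospital care depend much less on a scheduled call, and the halt applies to the whole trial, not to one arm.

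**Conclusion.** The point holds in a limited form. The described complication enquiry between surgery and T1 is unequal by arm, so adverse events reported under section 2.9 are liable to look more frequent in the intervention arm through detection alone, mainly non-serious ones. The direction follows from the text, provided that controls receive no equivalent enquiry described elsewhere. The size does not follow: the ratio of 1.3 to 3.3 rests wholly on assumed detection probabilities. The PHQ-9 comparison and the T1 ultrasound and HCG are untouched. This is a worthwhile, inexpensive improvement, not a defect in the main analysis.

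**What to change.** At T1, have the staff who already examine every woman complete one checklist with fixed wording in both arms, covering surgery to T1. It should ask about the symptoms named in the one-week contact, unscheduled visits or treatment elsewhere, and hospitalisation. Add it as a row in Table 1. State that any adverse event summary by arm uses this source only, and list separately the events found solely through the call or the AI logs. The reporting duty in section 2.9 and the intervention itself stay as they are.

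Fixed wording also gives some protection if the examiner guesses the allocation, since Phase 3 of section 2.5.4 has a researcher accompany intervention patients to the examination.

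The cost is one form page, a few minutes per woman and no extra staff. The downside is some recall error over two weeks. It may not be perfectly equal, because women already asked at one week could remember more, but the enquiry itself would be the same in both arms.

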**Intervention content:**

Send brief post-operative instructions via WeChat to guide patients in using Artificial Intelligence-Empowered Mobile Health.Monitor data in the system and provide feedback updates.

**Specific Methods:**

Check the Official Account function before 8:00 every day to ensure that the AI response is working properly.Send brief post-operative guidance and education via WeChat at 9:00 every day, and guide consultations through questions about common misconceptions. For example: “Is it true that you can’t eat fish after an abortion?” Please consult “Xiao Yu” (the name of the Artificial Intelligence-Empowered Mobile Health agent) for an authoritative answer!Review patient-AI interaction records by 9:00 PM daily, summarize key feedback for the attending doctor, and simultaneously update the knowledge base with missing content.

**Swanson’s Theory of Caring:** Being with, Maintaining belief.

**Intervention providers:** Researcher.

**Intervention content:**

Guide patients to express their emotions appropriately.Encourage patients to develop hobbies and interests.Encourage family members to accompany patients.Inform patients of follow-up examination arrangements and precautions.

**Specific Methods:**

Artificial Intelligence-Empowered Mobile Health provides patients who lack emotional outlets with humanized emotional release and real-time companionship support, filling the gap left by their reluctance to express themselves or insufficient family support.Artificial Intelligence-Empowered Mobile Health can provide recommendations for activities of interest and help patients plan their schedules, helping them avoid lying in bed alone, alleviating negative emotions, and solving their difficulties in choosing activities.Artificial Intelligence-Empowered Mobile Health solutions use human-like imagery and interactive entertainment features to provide alternative emotional support for patients living alone or lacking family support.Strengthen the connection between patients and researchers to identify serious issues and initiate timely medical interventions. Inform patients of follow-up appointment times, locations, procedures, required materials, and preparation requirements, such as fasting or holding urine.

**Phase 3: Follow-up to ongoing treatment**.

**Swanson’s Theory of Caring:** Knowing.

**Intervention providers:** Attending doctor, researcher.

**Intervention content:**

Conduct clinical examinations to assess recovery.Collect patients’ opinions on the study.

**Specific Methods:**

Conduct inquisition, physical examinations, and necessary auxiliary examinations, and promptly provide feedback and explanations of the results to patients.Collect patient responses and impressions regarding the use of Artificial Intelligence-Empowered Mobile Health through semi-structured interviews, and guide completion of follow-up questionnaires.

**Swanson’s Theory of Caring:** Doing for, Enabling.

**Intervention providers:** Researcher.

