**Figure 1 f1:**
[figure not shown]
Flow chart of patient recruitment and study implementation.

The study used a simple randomization method. The steps are as follows: first, in Excel, we used the RAND function to generate a number between 0 and 1. The function is invoked by entering “=RAND()” in any cell and pressing Enter. The generated number determines the group assignment for each patient: if the number is from 0 to 0.5 (excluding 0.5), the patient is assigned to the intervention group; if it is from 0.5 to 1 (excluding 0.5), the patient is assigned to the control group. If the number is exactly 0.5, the process is repeated until a valid random number is obtained.

The blinded method used in this study involves several categories of individuals:

Medical staff in the research department (blinded): responsible for patient recruitment, informing patients of admission and follow-up times and locations, and conducting basic biochemical and imaging examinations for admission and follow-up, they are unaware of patient group assignments.Investigators (blind): Their responsibilities are strictly limited to one-on-one data collection with patients; they do not participate in other research activities to ensure data specificity and accuracy. Investigators are unaware of patient group assignments.Data processing personnel (blind): They receive coded data (Group A/Group B) and are unaware of the specific assignment relationship between Groups A/B and the intervention or control groups.Patients (unblinded): The intervention group is guided by the researcher to follow the Artificial Intelligence-Empowered Mobile Health Official Account and instructed on its use. The control group does not receive this service.System administrator (unblinded): Responsible for online management and answering questions for patients in the intervention group; their service is limited to patients in the intervention group, as only this group receives the Artificial Intelligence-Empowered Mobile Health intervention.

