**Specific Methods:**

Study Introduction and Trust Building: During outpatient visits, the researcher and attending doctors jointly provide patients who meet the inclusion criteria and are willing to participate in the study with a comprehensive introduction to the study, thereby establishing an initial trust relationship with the patients.Establishment of Patient Information Records: For patients who meet the study criteria and are included in the study, the researcher guides them in completing electronic questionnaires via Questionnaire Star after signing the informed consent form. Basic medical conditions and laboratory results are recorded in the hospital’s medical record system.In-depth Interview Research: Researchers engage in in-depth communication with patients, asking questions such as “What do you think is the biggest problem you are facing right now?” and “What are your strongest feelings about abortion?” to gain a detailed understanding of the patients’ thoughts and needs.

**Swanson’s Theory of Caring:** Doing for, Enabling.

**Intervention providers:** Researcher.

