**Specific Methods:**

Contact the patient proactively before the follow-up examination to reconfirm the time, location, and examination items.Accompany the patient throughout the follow-up examination on the day of the appointment, explaining the environment and the purpose of each examination to alleviate any feelings of unfamiliarity.Pay attention to the patient’s emotions, provide patient companionship and positive support, and encourage them to face the future with optimism.

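### Data collectors are declared blind, yet the intervention section has its providers guide the follow-up questionnaires that carry the primary outcome

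*Protocol article*

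**What the plan says.** **Blinding (Section 2.1, list below Figure 1).** Of the investigators it says: "Their responsibilities are strictly limited to one-on-one data collection with patients; they do not participate in other research activities". It adds: "Investigators are unaware of patient group assignments". Patients are openly unblinded, and the same list shows the researcher on the intervention side: "The intervention group is guided by the researcher to follow the Artificial Intelligence-Empowered Mobile Health Official Account and instructed on its use".

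**Intervention (Section 2.5.4).** The first block of Phase 3 lists under intervention providers "Attending doctor, researcher". One of its methods is: "Collect patient responses and impressions regarding the use of Artificial Intelligence-Empowered Mobile Health through semi-structured interviews, and guide completion of follow-up questionnaires". A later Phase 3 block, with the researcher as provider, has this task: "Accompany the patient throughout the follow-up examination on the day of the appointment".

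**Study management (Section 2.9).** Investigators take participants one-on-one through a single electronic questionnaire and may explain items but not prompt answers. The same section says: "During the interview, investigators flexibly guide the conversation, listen attentively, and avoid subjective evaluations".

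**Outcome (Sections 2.6.1.1 and 2.6.2, Table 1).** The PHQ-9 is the primary outcome and comes from the baseline and follow-up questionnaires. The listed interview questions, the first of which asks which AI functions the patient used, concern the AI tool.

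**Control (Section 2.5.1).** Controls receive oral health education at enrolment, and their questions are answered. No provider role at follow-up is described.

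**The concern.** The PHQ-9 is self-reported by patients who know their arm. How it is collected is therefore one of the few remaining safeguards, and the protocol offers blinded collectors for that purpose. The intervention section assigns the same task to people who cannot be blind. The researcher teaches the patient to use the AI account, sends daily guidance, reviews her chats with it, and is with her at the follow-up visit.

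A patient who completes a depression scale with help from the person who has cared for her may answer differently from one helped by a stranger. If that happens in one arm only, the difference enters the treatment comparison. Neither the planned GEE nor the multiple imputation in Section 2.7 can remove it, because both take the recorded scores as given.

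**Working it through.** No figure in the protocol is in dispute here. The check sets the role descriptions side by side and then illustrates what a collection effect could do.

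**1. Who guides the follow-up PHQ-9?**
- Section 2.1: investigators, blind and confined to data collection.
- Section 2.5.4, Phase 3: the attending doctor and the researcher, as intervention providers.
- Section 2.9: investigators, with no distinction by arm.

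**2. Reading A: Section 2.5.4 governs.** The providers guide the questionnaire in the intervention arm. They know the arm, so the primary outcome is not collected by blinded staff there.

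**3. Reading B: Section 2.9 governs.** Investigators guide the questionnaire, but they also hold the interviews. Interviewing might pass as data collection, so the limit on duties may survive. The unawareness does not: an intervention patient who answers the listed questions discloses her arm. This affects only patients who are interviewed. It reaches the PHQ-9 only if the interview comes first, and no order is stated.

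**4. If researcher and investigator mean the same people,** the claim fails more plainly, since the researcher trains patients on the AI.

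**5. Control arm.** No passage says who helps controls with the follow-up questionnaire. The provider task appears only in the intervention section, which suggests a difference between arms without stating one.

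**6. Illustration.** Inputs from Section 2.3: SD 6 to 8, planned difference 5 points, 50 enrolled per group. Section 2.7 gives two-sided 5% tests. The shift b is an assumption, taken as 1 to 2 PHQ-9 points, that is 1/5 = 20% to 2/5 = 40% of the planned difference. Full follow-up is assumed.

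SE = SD·√(2/n). Rejection rate with no true effect = Φ(b/SE − 1.96) + Φ(−b/SE − 1.96).

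| SD | n per group | SE | b = 1 | b = 2 |
|---|---|---|---|---|
| 8 | 50 | 1.600 | 9.6% | 24.0% |
| 8 | 42 | 1.746 | 8.8% | 20.9% |
| 6 | 50 | 1.200 | 13.3% | 38.5% |

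For SD 8, n = 50, b = 1: b/SE = 0.625, and Φ(−1.335) + Φ(−2.585) = 0.091 + 0.005 = 0.096. The rate is the same whichever way the shift goes; only the favoured arm changes. The row with 42 uses the plan's size before allowance for losses. Whether 42 follows from the plan's formula is a separate question that does not affect this point.

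**The case against.** The strongest reply is that Section 2.9 already describes one standardised procedure for everyone, in which the patient scans a code, completes a uniform electronic form and is not prompted. Read alone, that passage is sound, and it may be what the sponsor intends. It does not remove the conflicting task in Section 2.5.4, and it brings its own difficulty by giving the interviews to the same role.

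Several stronger readings are tempting but not supported:
- **That the PHQ-9 is collected differently by arm.** This is inferred from where the task is placed. No passage describes the controls' procedure.
- **That patients are primed by an interview about the AI.** Section 2.4.2 selects interviewees on baseline PHQ-9, with separate consent and scheduled times. Order of listing is not order of the visit. The questions are also balanced: they ask about absent and negative effects as well as positive ones.
- **That the bias must favour the intervention.** A wish to please the provider would plausibly lower scores, but trust could also lead to fuller disclosure and raise them.
- **That baseline is affected too.** Phase 1 says "the researcher guides them in completing electronic questionnaires via Questionnaire Star after signing the informed consent form", but nothing shows that this is specific to one arm or follows allocation.

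It is also fair to say that blinded collectors would not remove all reporting bias from a self-report scale in unblinded patients. What stands is the contradiction over roles and the failure of the blinding claim as written.

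**Conclusion.** The protocol contradicts itself on who collects its primary outcome, and the statement that investigators are blind does not hold as written under either reading. That conclusion rests on the text alone.

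A difference in collection between arms is possible and should be excluded, but it is not established. The documents give neither the size nor the direction of any bias. The error rates of 9.6% to 24.0% (SD 8, 50 per group) follow wholly from an assumed shift of 1 to 2 points. They show that a modest collection effect could matter; they do not estimate one. The point should be settled before follow-up data are gathered, because the analysis cannot repair it afterwards.

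**What to change.** Reconcile Sections 2.1, 2.5.4 and 2.9:

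1. Remove the guiding of follow-up questionnaires from the providers' tasks in Phase 3 of Section 2.5.4.
2. State that in both arms the follow-up questionnaires are self-completed under the same blinded investigators, who are not intervention providers, before examination results are fed back and before any interview.
3. Assign the AI interviews to the already unblinded researchers, after the questionnaires, and amend Section 2.9 accordingly.
4. For baseline, state only that the questionnaires are completed before allocation and by the same procedure in both arms.

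If items 1 to 3 are not feasible, delete the claim that investigators are blind and report the outcome as self-reported with unblinded assistance.

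The cost is a change in the order of the follow-up visit and a reassignment of duties, with no new measurements. The documents give no staffing numbers, so whether present staff can cover this is for the sponsor to confirm.
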